#### Healthy controls

These subjects were only assessed at baseline (visit 2) to verify satisfaction of inclusion and exclusion criteria.

Once enrolled, blood samples were collected from the antecubital vein for DNA extraction for DNA methylation analysis for CGRP-related polymorphisms and for biochemical profiling. All subjects also underwent neuroimaging evaluation with 3 T Magnetic resonance imaging (MRI), including structural, resting state MRI (rsMRI), and Arterial Spin Labelling (ASL) using a standardised protocol provided by UKE.

The protocol design is illustrated in Figure 2, scheduled activities for subjects with migraine and healthy controls are summarised in Table 1.

**Figure 2 fig2:**
[figure not shown]
Graphical representation of the BIOMIGA trial and associated procedures. The study flow differentiates procedures for people living with migraine (blue line) and healthy controls (orange line).

### Data collection and management

#### Clinical profiling

The screening/baseline visit comprised the assessment of study eligibility, including a complete physical and neurological examination. A semi-structured interview was used to collect sociodemographic data, medical and headache history, detailed clinical characteristics, and current and past medication use.

Participants were instructed to fill out a prospective headache diary in paper format with daily entries throughout the baseline period and treatment period. Information about the abortive medication use was also acquired.

Participants were instructed to complete seven patient-reported outcome measures at screening, on Day 1 (first dose), and at the end of the treatment period. All questionnaires were administered in paper or digital format.

At baseline, disability was assessed with validated questionnaires in the national language of the participating centres. The questionnaires included the Migraine Disability Assessment (MIDAS) (30) and the Headache Impact Test-6 (HIT-6) (31); depression and anxiety symptoms with the Beck Depression Inventory-II (BDI-II) (32) and the Beck Anxiety Inventory (BAI) (33); health-related quality of life with the Migraine-Specific Quality of Life Questionnaire (MSQ) (34); and subjective cognitive impairment during migraine attacks with the Migraine-Specific Cognitive Impairment Scale (MIG-SCOG) (30). Information on medical comorbidities was also collected.

At all study visits, we recorded the use of concomitant medications and any adverse events (AEs) or serious adverse events (SAEs), which were graded according to the Common Terminology Criteria for Adverse Events (CTCAE) version 6.0 (35).

#### Biomolecular profiling

Blood samples (3 mL) were obtained from the cubital vein of participants, between 8:00 a.m. and 12:00 a.m. Patients were assessed during an interictal period and at least 12 h from the intake of an acute drug for migraine treatment. Venous blood was collected into one 9-mL K₃ ethylenediaminetetraacetic acid tube for plasma and two 8-mL sodium heparin Cell Preparation Tubes for mononuclear cell isolation.

For plasma levels of CGRP and cytokines, the K₃ tube with ethylenediaminetetraacetic acid (EDTA) was processed immediately after collection and centrifuged at 1500 × g for 15 min at room temperature; the plasma was separated.

For the expression of cytokine and CGRP mRNA, the cell preparation tubes were processed within 2 h of collection. The samples were centrifuged at 1,500–1,800 × g for 30 min at room temperature. Following centrifugation, the plasma was removed, and the mononuclear cell layer was transferred to 15 mL conical tubes that were free of DNase and RNase.

Fifteen milliliters of phosphate-buffered saline were added to the tube, gently mixed by inversion, and centrifuged again at 1,500 × g for 10 min. The supernatants were discarded, leaving the cell pellets for subsequent extraction.

Plasma aliquots were transferred into 1.5-mL polypropylene microtubes and stored at −80 °C for 4 months before assay. Mononuclear cell pellets from both conical tubes were pooled into a single 1.5-mL ribonuclease/deoxyribonuclease-free microtube, resuspended in 400 μL of Trizol reagent and stored at −80 °C until nucleic acid extraction. For centralised biomolecular analyses, both plasma samples and cell pellets in Trizol were shipped to the Pavia laboratory in temperature-controlled containers (dry-ice or liquid-nitrogen dry shippers), ensuring that a temperature of ≤ 80 °C was maintained throughout transport.

Pre-planned biomolecular analyses were performed at IRCCS Mondino laboratory, and they comprised the measurement of plasma α-CGRP, IL-1β, and TNF-α levels using a commercial enzyme-linked immunosorbent assay kit (α-CGRP, using OKEH00875 assay, Aviva Systems Biology; TNF-α, using RAB0476 assay and IL-1β using RAB0306 assay, by Millipore Sigma). Two measurements were performed for each sample, and the mean value was calculated and considered for statistical analysis.

In parallel, miRNA expression of CGRP, IL-1β and TNF-α was quantified in peripheral blood mononuclear cells by real-time quantitative polymerase chain reaction. The same peripheral profile of CGRP and pro-inflammatory cytokines was assessed at baseline in a group of healthy control subjects.

#### Pharmacogenetic profiling

For genomic analyses of DNA polymorphisms, venous blood was drawn by antecubital phlebotomy into a single 3-mL K₃-EDTA tube and stored at 4 °C for a maximum of 2 months before processing.

Samples were shipped to the central laboratory in Pavia in temperature-controlled conditions (chilled transport at 2–8 °C) for subsequent DNA extraction and genotyping.

Real-time polymerase chain reaction was used to identify single-nucleotide polymorphism variants of the calcitonin receptor-like receptor and some genes that modify receptor activity in all enrolled patients and healthy control subjects (36). Specifically, we selected single-nucleotide polymorphisms within RAMP1 (receptor activity–modifying protein 1) (37), CALCRL (calcitonin receptor-like receptor) and CRCP (CGRP receptor component protein), which together form and regulate the canonical calcitonin gene-related peptide receptor complex, as well as variants in GNAS, encoding the stimulatory alpha subunit of the heterotrimeric G protein that couples this receptor to intracellular signalling. These loci were chosen because prior evidence implicates them in migraine susceptibility and in the modulation of calcitonin gene-related peptide–mediated pathways, making them plausible candidates for influencing clinical response to calcitonin gene-related peptide–targeted preventive therapies (38).

#### Epigenetic profiling

For DNA methylation analyses, venous blood was collected into one 8-mL sodium heparin Cell Preparation Tube for mononuclear cell isolation. Samples were processed within 2 h of collection. Tubes were centrifuged at 1,500–1,800 × g for 30 min at room temperature, the plasma phase was removed, and the mononuclear cell layer was carefully transferred to a 15-mL deoxyribonuclease/ribonuclease-free conical tube. Phosphate-buffered saline was added to a final volume of 15 mL, the suspension was gently mixed by inversion and centrifuged at 1,500 × g for 10 min at room temperature. The supernatant was aspirated without disturbing the cell pellet.

The resulting mononuclear cell pellet in the deoxyribonuclease/ribonuclease-free conical tube was stored at −80 °C for a maximum of 4 months before DNA extraction. For centralised epigenetic analyses, frozen pellets were shipped to the Barcelona laboratory in temperature-controlled containers (liquid-nitrogen dry shipper or dry-ice shipper), ensuring maintenance of a temperature of ≤ 80 °C throughout transport.

Planned DNA methylation of CpG islands was quantified using the Infinium MethylationEPIC BeadChip (Illumina, Inc.) at Vall d’Hebron laboratories. All procedures were performed following the manufacturer’s recommended protocols. Briefly, 600 ng of total DNA was subjected to bisulfite conversion using the Zymo EZ DNA Methylation Kit. Processing of the EPIC v2 BeadChips was carried out using the automated Infinium HD Assay Methylation protocol (User Guide 15,019,519 v01) on a TECAN Freedom EVO robotic platform. BeadChips were scanned using the Illumina iScan system with Autoloader to generate .idat files, and data quality control was performed using GenomeStudio software (version 2011.1). Post-processing and downstream analyses are going to be reported in future publications.

#### Neuroimaging profiling

Magnetic resonance imaging was performed under standardised interictal conditions to minimise intra- and inter-individual variability with 3 tesla scanners. All participants had fasted for at least 3 h before the scan and refrained from coffee, tea and other stimulant drinks during the same interval. Scans were acquired when participants had been pain-free for at least 24 h and had not taken any acute migraine medication or benzodiazepines in the preceding 24 h; if a migraine attack occurred, imaging was rescheduled to a pain-free day. To further reduce intra-subject variability, each participant was scanned at approximately the same time of day at all visits.

Patient comfort and immobility were actively promoted. During resting-state functional imaging, the scanner-room lights were switched off, and participants were instructed to keep their eyes closed, remain awake and avoid focusing on any specific thought. The imaging protocol was acquired in a fixed order: high-resolution structural imaging (magnetisation-prepared rapid gradient echo), resting-state functional magnetic resonance imaging, and arterial spin labelling. The imaging protocol was set and harmonised between centres. When feasible, respiratory and cardiac signals (breathing, pulse and/or electrocardiogram) were recorded to allow correction of physiological artefacts in the resting-state functional data.

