This persistent gap in the identification of a single biomarker likely reflects the complex and dynamic nature of migraine biology – with distinct attack, pre−/post-dromal and interictal phases – the multiplicity of implicated mediators CGRP, PACAP38 and other neuropeptides, monoamines, inflammatory pathways, miRNAs, etc., and the involvement of both peripheral and central structures, together with marked interindividual variability of clinical expression (24). Methodological heterogeneity across studies – including differences in sampling paradigms, assay techniques, patient populations and outcome definitions – has further contributed to inconsistent findings and limited precision of biomarker estimates (15).

The advent of migraine-specific preventive therapies targeting the CGRP pathway offers an unprecedented opportunity to stratify patients according to response to a well-defined molecular mechanism and to link biomarkers to a precise pharmacological target (11). In parallel, advances in high-throughput and systems biology approaches allow the integration of multi-omic signatures with deep clinical phenotyping, neuroimaging and digital biomarkers, while sophisticated animal models continue to refine mechanistic understanding of CGRP-related neuroinflammation (24, 25). Recent work indicates that artificial intelligence and machine-learning methods can extract predictive patterns of response to anti-CGRP mABs from large, heterogeneous datasets, although current models remain preliminary, require external validation and are not yet applicable in clinical practice (26–29).

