##### Exclusion criteria

a headache frequency of more than 25 days/month in the last 3 months;presence of acute medication overuse according to ICHD-3 criteria in the 3 months prior to the enrolment;any other significant medical condition (including neurological disorders, severe psychiatric illness, or cardiovascular disease);history or evidence of drug, or alcohol abuse or dependence within 12 months before the baseline visit;pregnant or breastfeeding women;women of childbearing potential (defined as all women physiologically capable of becoming pregnant) not using a reliable contraceptive method;concomitant use of other migraine preventive drugs.

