Specific challenges concern the measurement of circulating CGRP. CGRP has been proposed as the most promising candidate biomarker in migraine, but studies measuring its concentrations in peripheral blood and other biofluids have yielded conflicting results, owing to differences in sampling timing, assay sensitivity and specificity, and the episodic nature of peptide release (15). Recent work has started to clarify pre-analytical stability, suggesting that plasma levels are robust under controlled conditions (49), yet there is still no consensus on clinically meaningful thresholds or on the optimal sampling paradigm. BIOMIGA mitigates some of these issues through rigorous standard operating procedures and central laboratory analyses, but limited time-point measurements may not fully capture individual calcitonin gene-related peptide dynamics and could under-estimate within-person variability. Secondarily, despite evaluating patients in a pain-free state, patients living with CM determine the difficulty in having fully pain-free days within the allowed window of access, therefore possibly determining a higher variability of CGRP level or functional connectivity at the MRI scan between the ictal and interictal phases.

Other limitations are inherent to the complexity of the biomarker programme and to the application of ML approaches to high-dimensional, multimodal data. The large number of clinical, neuroimaging and molecular variables relative to the sample size increases the risk of overfitting and of identifying spurious associations, even when structured feature-selection strategies, class-imbalance handling and internal validation procedures are applied. Although BIOMIGA adopts advanced ML methodologies, including penalisation techniques and cross-validation frameworks, the resulting predictive models should therefore be regarded as exploratory and hypothesis-generating.

In addition, the absence of an independent external validation cohort limits the immediate generalisability of the proposed models. Performance estimates derived from internal validation approaches, such as out-of-bag estimation and cross-validation, may remain optimistic in the context of complex, multicentric datasets. Replication in larger, independent cohorts will be essential to confirm the robustness, stability and clinical relevance of the identified biomarker signatures.

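### At visit 5, super responders and full non-responders are sampled at systematically different distances from their last headache, and no covariate named in the article separates this from a change in the biomarker

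*Protocol article*

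**What the plan says.** **MRI** (Neuroimaging profiling): "Scans were acquired when participants had been pain-free for at least 24 h". A gap of the same length applies to acute drugs and benzodiazepines. The rule after an attack is: "if a migraine attack occurred, imaging was rescheduled to a pain-free day".

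**Blood** (Biomolecular profiling): "Patients were assessed during an interictal period and at least 12 h from the intake of an acute drug for migraine treatment". No number of pain-free hours is given.

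**Phases** (Background): the article describes migraine biology as dynamic, "with distinct attack, pre−/post-dromal and interictal phases", and says that circulating CGRP rises in attacks and correlates with headache frequency.

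**Who is re-measured** (Interventions): epigenetic, biomolecular and imaging measures are repeated at visit 5 only in super responders (SR, at least 75% reduction in monthly headache days) and full non-responders (FNR, less than 25% reduction).

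**Planned use** (Efficacy endpoint analyses): longitudinal structural and functional MRI differences are compared among response groups. Plasma CGRP, IL-1β and TNF-α and their mRNA are followed over treatment and correlated with headache frequency, acute medication and disability.

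**Adjustment:** Mitigation of confounding factors lists baseline monthly migraine days and acute medication intake, among others, as potential confounders. The imaging covariates named are scanner site, age, sex and head motion. None is a timing variable for the individual sample.

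**Limitation conceded** (Limitations and future directions): "patients living with CM determine the difficulty in having fully pain-free days within the allowed window of access", which the article says may raise the variability of CGRP and functional connectivity.

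**The concern.** Both windows set a minimum gap since the last pain or the last acute drug. Beyond that minimum, time since the last attack is free to vary, and it is shorter in patients with more headache days. A pain-free day can also be a post-dromal or pre-dromal day, which the Background treats as distinct from interictal.

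At visit 5 this matters most, because the two groups sampled are defined by how many headache days they had in the final four weeks. A marker that tracks only attack phase would differ between SR and FNR with no drug-related change in the marker. The contrasts at stake are plasma CGRP, cytokines, mRNA, resting-state fMRI and ASL. The Limitations section describes the problem as extra variability in chronic migraine (CM), so a reader would expect associations to be diluted. A shift that runs with the response label can also create one.

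**Working it through.** The article states no figure on this point, so there is none to reproduce. The numbers below show direction and rough size under stated assumptions.

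**Inputs from the article**
- Lowest eligible frequency: 8 headache days per month (Inclusion criteria).
- Highest eligible frequency: 25, since the exclusion is "a headache frequency of more than 25 days/month in the last 3 months".
- SR: at most 25% of baseline days remain. FNR: more than 75% remain.
- Response period: final 4 weeks, taken as 28 days.

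**Separation of the groups.** If run-in frequency lies in the eligible range, an SR has at most 25 × 0.25 = 6.25 days and an FNR more than 8 × 0.75 = 6 days. The groups therefore barely overlap in week-12 frequency whatever the baseline. At any one baseline they cannot overlap.

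**Assumed model.** Headache days follow a two-state daily chain with p = days/28 and lag-1 correlation r. The article gives no data on clustering, so r = 0 and r = 0.5 are both shown.
- Chance that a headache-free day is followed by a headache day: a = p(1 − r).
- Mean days since the last headache, given a headache-free sampling day and a headache-free day before it (the MRI rule at day level): 1 + 1/a.

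**Worked case, 16 days at baseline, boundary values 4 and 12, r = 0**
- SR: p = 4/28 = 0.143; next-day headache 14%; 1 + 1/0.143 = 8.0 days.
- FNR: p = 12/28 = 0.429; next-day headache 43%; 1 + 1/0.429 = 3.3 days.

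| Baseline days | SR vs FNR days at week 12 | r | Next-day headache, SR vs FNR | Mean days since last headache, SR vs FNR |
|---|---|---|---|---|
| 8 | 2 vs 6 | 0 | 7% vs 21% | 15.0 vs 5.7 |
| 8 | 2 vs 6 | 0.5 | 4% vs 11% | 29.0 vs 10.3 |
| 16 | 4 vs 12 | 0 | 14% vs 43% | 8.0 vs 3.3 |
| 16 | 4 vs 12 | 0.5 | 7% vs 21% | 15.0 vs 5.7 |
| 25 | 6.25 vs 18.75 | 0 | 22% vs 67% | 5.5 vs 2.5 |
| 25 | 6.25 vs 18.75 | 0.5 | 11% vs 33% | 10.0 vs 4.0 |

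Clustering halves the next-day percentages, but their threefold ratio stays if r is the same in both groups. Boundary values give the smallest contrast at each baseline.

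**Does the listed confounder remove it?** No. Each row of the table holds baseline frequency fixed and the difference is still there.

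**Baseline samples, r = 0.** If responders and non-responders both have 14 days, next-day headache is 50% vs 50%. With a gap of 2 days it is 50% vs 57%, and with a gap of 4 days 50% vs 64%. There is no timing difference unless the groups differ in baseline frequency.

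**The case against.** The strongest case against has four parts.

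1. **Timing is controlled.** MRI needs 24 hours free of pain and drug, with rescheduling. A reader might infer that the plan ignores distance to the last attack altogether; the text does not support that. What stands is that the windows are minimums and that blood has no stated pain-free hours.

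2. **Frequency is handled and the problem disclosed.** Baseline monthly migraine days are a listed confounder and the limitation is conceded for CM. This helps at baseline. It does not reach visit 5, and variability is an incomplete description there. The article defers image processing details to later publications, and a fuller protocol or analysis plan may name a timing variable. That is a reason to check those documents; it does not correct the limitation as published.

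3. **The prediction models use baseline data.** A reader might infer that baseline responder signatures are already contaminated by headache frequency. The article does not support this: response is a percentage change from each patient's own baseline, and baseline frequency by response group is not reported. Germline polymorphisms cannot be affected at all.

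4. **Adjustment can itself do harm.** Days since last headache at week 12 is a consequence of the frequency that defines the groups, so adjusting for it may remove genuine response-related change. Days to next headache after the baseline sample fall after the first dose, if sampling was at visit 2, and are related to outcome. Healthy controls have no diary in Table 1. All of this stands and limits the remedy.

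A reader might also infer that rescheduling pushes the scans of full non-responders later after the last dose. The article gives no data on that.

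**Conclusion.** The point holds for the visit 5 comparisons of phase-sensitive markers between super responders and full non-responders. Sampling distance from the last headache differs between these groups because of how they are defined, and baseline monthly migraine days cannot correct it. In the illustrative case the mean is 8.0 vs 3.3 days since the last headache and the chance of next-day headache 14% vs 43% with independent days, or 15.0 vs 5.7 days and 7% vs 21% with lag-1 correlation 0.5.

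These sizes rest on the daily chain, a 28-day month, boundary values of response, equal clustering in both groups, and counting every headache day alike. The direction does not depend on the exact values. How much any marker shifts with phase is not known from the article, so this is a possible bias of unknown size, not a demonstrated one.

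For baseline responder analyses the concern is conditional on a difference in headache frequency between response groups. It is worth acting on now, since the article says that analysis of the stratified groups is still under way.

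**What to change.** **Visit 5.** From the daily diary (Clinical profiling), derive days since the last headache day for each blood sample and scan, and derive days since the last dose. Report SR versus FNR contrasts of plasma CGRP, cytokines, mRNA, resting-state fMRI and ASL unadjusted. Beside them give two sensitivity analyses: one adjusted for days since last headache, and one limited to samples at least 2 days after the last headache day.

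**Baseline responder analyses.** Use only pre-dose timing, that is days since last headache, together with baseline headache frequency. Do not use days to next headache. Do not apply timing covariates to patient-control comparisons.

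**Text.** In Limitations and future directions, state a possible bias aligned with response group at visit 5, in addition to variability in CM.

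**Reconcile.** Table 1 places baseline blood and neuroimaging at visit 1, while the visit 2 description places them at visit 2. At visit 1 the diary had not started, so days since last headache could not come from it.

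**Cost.** No new data or visits. The adjusted analysis may remove real response-related change and does not capture the pre-ictal phase. The 2-day limit loses high-frequency patients: in this model a share a of headache-free days follow a headache day, so in the 16-day case it would drop about 14% of SR and 43% of FNR blood samples (7% and 21% at r = 0.5). It adds little for MRI, where the 24-hour rule already comes close to it, and the means of 8.0 and 3.3 days still apply in the set that remains. Both therefore stay as sensitivity analyses.
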